This study aims to investigate whether empirical use of an antibiotic with greater antimicrobial sensitivity (ceftriaxone) than standard of care (ampicillin plus gentamicin) will reduce mortality among CLHIV and CHEU admitted with severe acute malnutrition at Mwanamugimu Nutrition Unit, Mulago Hospital. Secondary objectives include: to compare the length of hospitalization, weight-for-height, weight-for-age and height-for-age z-scores between ceftriaxone vs. standard of care (ampicillin and gentamicin) treatment arms. These anthropometric indices and length of hospitalization are hypothesized to be affected by infection related morbidity which may be influenced by the antibiotics received. Other secondary objectives include: to ascertain the frequency of different bloodstream bacterial pathogens and their antimicrobial sensitivities; to ascertain the prevalence of, and factors associated with, HIV-infection among children admitted with severe acute malnutrition at Mwanamugimu Nutrition Unit; and to evaluate the pharmacokinetic (PK) parameters of LPV/r among severely malnourished CLHIV.

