### Study Population

Three hundred children aged 1 month to 5 years (76 CLHIV and 224 CHEU) whose caretakers provide informed consent will be randomized to receive ceftriaxone (*n* = 150) or ampicillin plus gentamicin (*n* = 150). The 1 month to 5-year age group has been selected because it is the most affected by severe acute malnutrition and constitutes over 95% of admissions at Mwanamugimu Nutrition Unit. Also, the 1:3 ratio of CLHIV to CHEU in this sample is reflective of the current proportions of CLHIV and CHEU admitted at Mwanamugimu Nutrition Unit.

Three hundred randomized children provide >80% power to detect reductions in mortality from 28% (average across CLHIV and CHEU in preliminary audits at the unit) to 14% (50% relative reduction; absolute 14% improvement), allowing for 10% non-compliance/loss-to-follow-up (leaving hospital without official discharge) in each group. When half the participants have been enrolled (*n* = 150), the data safety monitoring board (DSMB) will review the preliminary data to determine if these estimates are appropriate. In addition, at least 280 severely malnourished children and their mothers will be tested for HIV at admission; any positive children will also be eligible to participate in the clinical trial. Two hundred eighty children provide 80% power to determine the prevalence of HIV-infection, using the prevalence of HIV-infection of 24% obtained in the probisam study in Mwanamugimu in 2013 (10), as a reference. The CLHIV in the clinical trial on LPV/r will take part in the pharmacokinetic sub-study providing 3 sparse PK samples each.

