### Study Procedures

All severely malnourished children and their mothers will have rapid HIV antibody tests on admission as per routine practice; at least 280 children will participate in the cross-sectional study. Children under 18 months of age with positive HIV results will have blood taken for DNA PCR. The children who test positive or whose mother's test positive (i.e., are CHEU) will be eligible for enrolment into the trial. Participant enrolment will be done between 9.00 am and 4.00 pm from Monday to Friday to allow for blood samples to be taken to the laboratories on the day of enrolment. HIV rapid testing will be done at the unit (Mwanamugimu); HIV DNA PCR at the Baylor Uganda center of excellence (COE) laboratory at the Mulago Hospital Complex. At enrolment, anthropometry and a physical examination will be done; resuscitation will be provided as needed and a blood sample will be taken off for blood culture. The blood culture and sensitivity will be done in the Microbiology laboratory at the Makerere University College of health Sciences (MakCHS). After all enrolment procedures have been done, children will be randomized to ceftriaxone vs. ampicillin/gentamicin. The children will then receive antibiotics as randomized for 1 week together with other routine care. At day 8 (on completion of study medication), the children will be evaluated to ascertain any events that may have occurred and document administration of the study medication. They will then be followed up until discharge/death whichever occurs first. ART naïve CLHIV will initiate ART during admission while ART-experienced children will continue their regimens; both groups will receive daily cotrimoxazole throughout follow-up. The eligible CLHIV on LPV/r (target number – 76) will have 3 sparse PK samples taken at least 2 weeks after ART initiation and at least 1 week after admission to hospital (after they have completed the stabilization phase of treatment); the samples will be taken over 2–3 days depending on what is physiologically possible for the children. The samples will be collected from the study population to cover three time points. The child will take an observed morning dose and then sampling will be done at 3 h, at 6 h and at 12 h (just before the evening dose). LPV concentrations in the plasma samples will be determined using ultra performance liquid chromatography with ultraviolet detection in the Department of Pharmacology and Therapeutics, MakCHS. All laboratories are on the same location on Mulago hill, within a 1 km radius. During admission, the mothers will be interviewed to ascertain sociocultural/ system factors related to antenatal care attendance, prior HIV testing, knowledge and access to PMTCT services, infant feeding practice and ART adherence (theirs and the children's as applicable). Some of the mothers (~20) will be asked to participate in in-depth interviews. These will be consecutively enrolled until data saturation. These interviews will be tape recorded, transcribed verbatim and then translated into English where applicable. Any adverse events that develop will be managed according to the treatment protocols of Mwanamugimu Nutrition Unit/ Mulago Hospital. The principal investigator will be notified of these events within 24 h, who will in turn inform the trial sponsor within 24 h; and the Research Ethical Committee (School of Medicine Research Ethical Committee at Makerere University) within 7 days; and Uganda National Drug Authority within 7 days, as per the local research guidelines.

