### Data Management and Statistical Analysis

A database will be designed to capture the patient data from the study tools. Data will be checked for completeness before entry into the database. The database will be backed up on a daily basis. The study tools for each patient will be put in separate folders and kept in lockable cabinets. The primary outcome will be in hospital mortality. Secondary outcomes will be: length of hospitalization (for those that are followed up till discharge); as well as weight-for-height, weight-for-age and height-for-age z-scores during follow up. The change in these anthropometric indices (z-scores) from admission to discharge will be determined, while controlling for the number of days of hospitalization. Another secondary outcome will be the distribution/antimicrobial sensitivity of pathogens.

Mortality (and other time-to-event data) will be compared between randomized groups using Kaplan Meier curves and Cox proportional hazards regression. WHO reference ranges will be employed to determine the anthropometric z-scores which will be analyzed using linear regression. Other categorical factors will be compared between randomized groups using chi-squared and exact tests, and continuous data using rank-sum tests. The statistical analyses will be performed in STATA version 15 (Stata Corporation, Houston, Texas).

Qualitative data from the in-depth interviews of the mothers will be analyzed using a content thematic approach, using *NVivo software*. We will enroll mothers and perform ongoing analysis until there is saturation of data.

For primary analysis in the PK sub study, sparse PK samples will be obtained from approximately 76 CLHIV. Using NONMEM version 7.3, PK-PD modeling and simulations will be performed to determine primary PK parameters, measures of plasma drug exposure and the dosing requirements.

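### The trial is sized on the risk of dying in hospital (28% vs 14%), but the only analysis named for mortality, Kaplan-Meier and Cox with follow-up ending at discharge, by default compares daily death rates on the ward

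*Protocol article*

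**What the plan says.** Four statements in the protocol article bear on this point.

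- **Outcome and method** (Data Management and Statistical Analysis): "The primary outcome will be in hospital mortality". No fixed day is attached to it. For the comparison: "Mortality (and other time-to-event data) will be compared between randomized groups using Kaplan Meier curves and Cox proportional hazards regression". The tests for proportions go elsewhere: "Other categorical factors will be compared between randomized groups using chi-squared and exact tests".
- **End of follow-up** (Study Procedures), after the day-8 evaluation: "They will then be followed up until discharge/death whichever occurs first". Table 1 shows no contact after discharge.
- **Sample size** (Study Population): "Three hundred randomized children provide >80% power to detect reductions in mortality from 28"%, and the sentence continues "to 14% (50% relative reduction; absolute 14% improvement". It allows 10% per group for non-compliance or loss. Allocation is 150 per arm.
- **Length of stay** (Introduction, secondary objectives): "These anthropometric indices and length of hospitalization are hypothesized to be affected by infection related morbidity which may be influenced by the antibiotics received".

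The article states no censoring rule for live discharge, no competing-risk method and no common time horizon for mortality.

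**The concern.** A child discharged alive can no longer die in hospital during that admission, so live discharge is a competing event for the primary outcome. When follow-up stops at discharge and the data go into standard Kaplan-Meier and Cox procedures, such children are censored at discharge unless a rule keeps them in the risk set. Two things follow.

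- The Cox hazard ratio compares deaths per day at risk on the ward. The sample size compares the fraction of children who die in hospital. The two agree only under particular timings of death and discharge.
- One minus Kaplan-Meier estimates mortality as if nobody could be discharged. It therefore reads higher than the proportion who actually die in hospital.

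The article's own hypothesis is that the antibiotic may alter length of stay, so the gap between the two quantities may differ by arm. Mortality is the decisive result, and the Discussion concedes that the assumed halving is unusual and that a much larger trial would be unworkable. There is little power to spare.

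**Working it through.** **Inputs from the article:** risks 28% and 14%; 150 per arm; 10% allowance, so 150 × 0.90 = 135 per arm. **Assumed, because not given:** two-sided alpha of 0.05, the timing of deaths, and length of stay.

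**1. The plan's own figure.** Two-proportion test, pooled normal approximation, mean risk 0.21:

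- SE under the null = √(2 × 0.21 × 0.79 / 135) = 0.0496
- SE under the alternative = √((0.28 × 0.72 + 0.14 × 0.86) / 135) = 0.0488
- Power = Φ((0.14 − 1.96 × 0.0496) / 0.0488) = Φ(0.88) = 81.0%

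This reproduces the stated figure of more than 80%. In reverse, 132 per arm are needed, and 132 / 0.90 = 147 per arm, or 294 in all against 300 planned. The figure is consistent with a comparison of two cumulative risks.

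**2. What Cox estimates when discharge censors.** Under constant rates, in-hospital risk = death rate / (death rate + discharge rate). Hence

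HR = (0.14 / 0.28) × (mean time to exit, control / mean time to exit, ceftriaxone).

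With risks fixed at 28% and 14%, the HR is 0.50 at equal stay, 0.50 / 0.8 = 0.625 if the ceftriaxone stay is 20% shorter, and 0.50 / 1.25 = 0.40 if it is 25% longer. The risk of dying is the same in all three cases, but the HR is not.

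**3. Power by simulation.** True risks 28% vs 14%, 135 per arm, log-rank (Cox score) test with censoring at discharge. Comparing proportions gives about 82% in every row.

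| Assumed timing (control vs ceftriaxone) | Log-rank/Cox power |
|---|---|
| Discharge after day 7, mean survivor stay 16 vs 13 d, deaths mean day 3 | about 79% |
| Same, deaths mean day 10 | about 45–51% |
| Discharge after day 7, equal stay, deaths mean day 3 to 10 | 76–83% |
| Constant exit rates, equal stay | 70% |
| Constant exit rates, median stay 14 vs 11 d | 36% |
| Constant exit rates, ceftriaxone stay 25% longer | 91% |

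The 45–51% spread comes from how the discharge times are set up, for example whether the earliest discharge is just after day 7 or on day 8.

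**4. Equal in-hospital risk (21% in both arms).** With discharge from day 8 and stay of 16 vs 13 days, the log-rank test rejects in 5%, 6%, 9% and 12% of trials for mean death day 3, 5, 7 and 10. With constant rates and median stay of 14 vs 11 days it rejects in about 15%. The proportion test stays near 5%.

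**5. Kaplan-Meier against cumulative incidence.** Control arm, 28% eventual risk, constant rates, median stay 14 days, at day 28:

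- 1 − KM = 1 − exp(−0.28 × ln 2 / 14 × 28) = 32%
- Cumulative incidence = 0.28 × (1 − exp(−ln 2 / 14 × 28)) = 21%

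With early deaths (mean day 5) the corresponding figures are 33% and 28%.

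**The case against.** Several objections have force.

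- **Cox censored at discharge is a legitimate analysis.** A reader might infer that the test is invalid because it needs non-informative censoring. It does not: it estimates a cause-specific hazard. The assumption is needed only to read the hazard ratio or the Kaplan-Meier curve as a statement about in-hospital risk. Likewise, rejection above 5% at equal in-hospital risk is not a type I error for the cause-specific hypothesis, because the daily death rates do differ there. What remains is a mismatch of estimand.
- **The large losses need an implausible discharge pattern.** Constant exit rates with median stays of 14 and 11 days would send home 1 − 0.5^(7/14) = 29% and 1 − 0.5^(7/11) = 36% of survivors by day 7. The article plans a one-week course and a day-8 evaluation, and expects PK sampling in about the second week. Discharge mainly after day 7 is the better assumption, and the loss is then smaller.
- **The direction is not known.** The article says only that antibiotics may influence stay, not that ceftriaxone shortens it. A longer stay would raise Cox power.
- **Censoring at discharge is not written.** It is the default reading of the follow-up and analysis sections together. An analysis plan that is not shown could keep live discharges event-free to a common horizon and still use Cox.

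None of this removes the point. The article does name a method for mortality and directs the tests of proportions to other factors, so the mismatch lies in what it states and not in a detail left out.

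**Conclusion.** The point holds as a mismatch between endpoint and sample size on one side and the stated analysis on the other. It should be fixed. The trial is sized to compare the risk of dying in hospital; the named analysis, on its default reading, compares death rates among children still admitted, and its survival curves would overstate in-hospital mortality.

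The size is conditional. With discharge after day 7 and mean survivor stay of 16 vs 13 days, power runs from about 79% (early deaths) down to about 45–51% (later deaths), against about 82% for proportions. With equal stay and the same discharge pattern the loss is small. These timings are assumptions, and the article supplies none.

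A reader might go further and infer that the primary test will probably miss a true halving of mortality, or will point to harm. The documents do not support that. It requires a marked shortening of stay with ceftriaxone together with late deaths or constant exit rates, and the article gives neither the direction nor the timing. The sample size calculation itself is not at fault.

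**What to change.** In Data Management and Statistical Analysis:

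1. Make the primary analysis the intention-to-treat comparison of the proportion dying in hospital, counting live discharge as survival, and report the risk difference and risk ratio with 95% confidence intervals.
2. Replace the Kaplan-Meier plot for mortality with the cumulative incidence of in-hospital death, with live discharge as a competing event.
3. Keep the Cox model as a secondary analysis, labelled as a cause-specific hazard with censoring at discharge.

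The cost is wording only: no added patients and no new data. The planned 300 then match the analysis (81.0% by formula at 135 per arm). The downside is that the headline becomes a risk difference or ratio instead of a hazard ratio. How to count children who leave without official discharge is a separate missing-data question and is not part of this point. The change should be made before any unblinded comparison.

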### Ethical Considerations

The research protocol has been approved by the Makerere University School of Medicine Research Ethical Committee (REC. REF. 2020 - 165) and the Uganda National Council of Science and Technology (REF. HS1277ES). Regulatory approval was obtained from the Uganda National Drug Authority (NDA) (REF. CTC. 0168/2021). Administrative clearance was obtained from Mulago Hospital (REF. MHREC. 1942). All mothers of the participating children will provide written informed consent, using the consent documents in English and local 5 local languages (Luganda, Runyoro-Rutooro, Luo, Ateso and Swahili), as appropriate. The data collected will be kept under lock and key and saved in a secure database. Published patient data will not have names and confidentiality will be ensured throughout the study. All blood sampling done (including PK sampling) will be within recommended volumes taken during the specified period among malnourished children (21). Individual patient results will be provided to the Mwanamugimu Nutrition Unit staff for care as needed.

### COVID-19 Risk Management Plan

The trial is being implemented during the SARS-CoV-2 (COVID−19) pandemic. It is therefore imperative that efforts are made to protect the participants and the study staff from contracting the COVID-19 infection. Also, in case any of the participants or the study staff develops COVID-19 infection, they will be referred to the COVID-19 treatment unit of Mulago hospital for management. Personal protective equipment such as face masks, hand sanitizers and access to COVID-19 vaccination will be provided to study staff and participants, building on what is provided by Mulago hospital and the Uganda ministry of health. These measures are captured in an approved study risk management plan and standard operating procedures (SOPs). The plan will also include how the potential effects from the pandemic, such as slow recruitment due to reduced patient numbers in hospital, reduced workforce, lockdowns affecting movement, will be handled to ensure successful implementation of the study.

## Discussion

There is no published comparison of ceftriaxone vs. ampicillin/gentamicin (standard of care) in rates of mortality among CLHIV and CHEU admitted with severely acute malnutrition. This study provides the opportunity to evaluate it. This is important because infection-related mortality in this population is very high. It is also important to ascertain whether there has been a change in the pattern of organisms isolated from blood cultures and their antimicrobial sensitivities. In this study, ceftriaxone will be used empirically. Whilst it is possible that this could lead to adverse events such as diarrhea, skin rash and hypersensitivities, it is unlikely that these will occur more frequently than in CHUU or well-nourished children (13). There are also concerns regarding development of resistance, but benefits from reducing mortality may outweigh the risk of development of resistance. These risks and benefits however need to be formally evaluated.

In 2013, WHO recommended the “option B plus” strategy for prevention of mother to child transmission of HIV (PMTCT). Universal ART is recommended for pregnant women and nursing mothers living with HIV and the infants receive antiretroviral drug prophylaxis as part of comprehensive care (22). This not only has the potential to reduce HIV transmission to infants to <5% at 1 year, but could also improve the survival of CHEU (23, 24). Despite Uganda adopting the strategy in 2013, HIV-infected young infants continue to present to health units, and increasing numbers of CHEU are also presenting with poor outcomes when hospitalized (4). Therefore, ascertaining whether there has been a significant change in the prevalence of HIV-infection among children presenting with severe malnutrition in the option B plus era, while determining the social/structural factors associated with acquisition of HIV despite availability of PMTCT, will be useful as we aim to eliminate mother to child transmission of HIV.

Malnourished CLHIV have been reported to have poor outcomes on ART (11, 12); part of the explanation could be that the doses of antiretroviral drugs determined with well-nourished children may not be appropriate for the severely malnourished children who are known to have an altered physiology. For example, the drug levels in individuals are affected by the protein binding capacity of the drugs and it is known that malnourished children have low levels of protein (albumin) (25), implying that for the drugs that are highly bound to protein there would be a lot of free drug in malnourished children with a potential to cause an excess of adverse events. Examples of such drugs are lopinavir and ritonavir which are 98–99% bound to the blood plasma proteins albumin and alpha-1-acid glycoprotein (26). The Ugandan recommended alternative first line ART regimen for HIV infected children, is abacavir+lamivudine+lopinavir/ritonavir. Lopinavir/ritonavir (LPV/r) is also a key alternative drug in second-line regimens (18). In this project, we will investigate the pharmacokinetics of LPV/r among the severely malnourished children on ART, thereby providing an opportunity to test the hypothesis that severely malnourished children are ineffectively dosed according to the Ugandan guidelines, which does not differentiate well-nourished from malnourished children. It is possible that the severely malnourished children are exposed to toxic levels of free drug given the low level of albumin and drugs with high protein binding capacity. We will obtain sparse PK samples from the children while stable, likely in the second week of hospitalization, with the volumes of blood collected being those that are physiologically safe, such as those provided in a review of safe limits to volume by Howie SR (21). The study will also build on the work on PK and acceptability of LPV/r pellets in the CHAPAS 2 trial where bioequivalence between the pellets and syrup was demonstrated and the pellets were highly acceptable (27) and the follow on and ongoing implementation study of the LPV/r pellets (LIVING study) (28); as well as the LOLIPOP study evaluating the PK and acceptability of the 4 in 1 (abacavir+lamivudine+lopinavir/ritonavir) sprinkle formulation (29). Dolutegravir based regimens are becoming increasingly available and it is possible during the study period there are children that will be on dolutegravir. Dolutegravir PK will be considered among these children.

While the study will compare length of hospitalization and anthropometric z-scores between the two study arms as secondary outcomes, it will be difficult to control for social factors, which is a limitation of the study. Another limitation is that there may be children over the age of 18 months whose mothers are dead or unavailable. If these children test HIV negative, when their mothers were HIV infected, they will be taken as CHUU instead of CHEU, and will therefore be wrongly excluded from the study. On the other hand, a child over the age of 18 months may test HIV negative, while the mother tests HIV positive. Such a child will be taken as CHEU. However, the mother may have had a recent acquisition of HIV, and the child may not have necessarily been exposed to HIV. This child would wrongly be included in the study. We expect that children in these two scenarios will be very few. Furthermore, to obtain the sample size of 300, we made the assumption that the intervention would make a 50% relative reduction in mortality. While this is unusual, it is possible; on the other hand, a significantly smaller difference would result in a sample size that would make it logistically untenable to conduct the study.

The findings of this study in general will provide insights into designing protocols aimed at improving treatment outcomes, particularly reduced mortality, not just in CLHIV/CHEU but also overall mortality among severely malnourished children. Secondly, given that among CLHIV, the malnourished are at an increased risk of mortality (12), strategies that reduce mortality among severely malnourished CLHIV would result in an overall reduction in mortality among CLHIV.

